**Fig. 1 Fig1:**
[figure not shown]
Standard Protocol Items: Recommendations for Interventional Trials (SPIRIT) figure. *CCT* Compensatory Cognitive Training, *HRQoL* health-related quality of life, *SE* Supported employment

**Fig. 2 Fig2:**
[figure not shown]
Flowchart for the study protocol. *CCT* Compensatory Cognitive Training, *NAV* Norwegian Labor and Welfare Service, *TBI* Traumatic brain injury

### Study setting

Participants will be recruited from OUH and from general practitioners’ practices. OUH is the trauma referral center for the southeastern region of Norway and has a population base of more than half of the Norwegian population (i.e., 2.9 million). A feasibility study was conducted in the spring of 2017; recruitment for the RCT began in July 2017; and recruitment will continue until the required sample size has been achieved.

### Eligibility criteria

The study population will consist of patients with mild to moderate TBI as assessed by a Glasgow Coma Scale (GCS) score of 10–15, loss of consciousness (LOC) for < 24 h, and posttraumatic amnesia (PTA) for < 7 days [25]. Confirmation of the diagnosis of mild TBI will be done by documenting that acute symptoms adhere to the American Congress of Rehabilitation Medicine’s definition of mild TBI [30]. This will be either extracted from preexisting medical records or established at the time of screening for study eligibility. Patients will be considered eligible for study inclusion if they are employed in a minimum 50% position at the time of injury and are sick-listed at the 50% or higher level because of postconcussive symptoms 2 months postinjury as assessed by the Rivermead Post-Concussion Symptoms Questionnaire [31]. Participants will be aged 18–60 years and reside in Oslo or Akershus County. Patients with a history of severe psychiatric or neurological illness, active substance abuse, or inability to speak and read Norwegian will be excluded.

### Patient characteristics

The following sociodemographic variables will be recorded: age, sex, marital status, living conditions, educational level, description of preinjury employment, workplace, and work stability (days on sickness benefits 1 year prior to the injury). The Readiness for Return to Work scale [32] will be applied at baseline to assess the participants’ perceptions regarding RTW. To measure the impact of the work environment on the RTW process, the Copenhagen Psychosocial Questionnaire (COPSOQ) short version [33] will be applied at baseline. Medical variables include injury characteristics and clinical severity (GCS, LOC, PTA), neuroimaging results, length of hospitalization, medical treatment modalities, postconcussion symptoms, fatigue, and insomnia.

### Outcomes

The primary outcome measures are work participation as measured by the proportion of participants who have returned to work at 12-month follow-up and length of time before return to work (in days), work productivity (hours worked, work-related changes [i.e., reduced productivity, increased supervision, work content changes], and work stability [i.e., sickness absence after initial RTW and throughout the study period]). To provide descriptive information and group comparisons, an IQ estimate (Vocabulary, Similarities, Block Design, and Matrix Reasoning subscales of the Wechsler Adult Intelligence Scale–Fourth Edition) will be included at baseline (T1) only [34].

Postconcussive symptoms and quality of life will be used as secondary outcome measures at all time points (T1–T4), whereas outcome will also be measured in the domains of fatigue, sleep, emotional distress, self-efficacy, and cognition. The instruments that will be applied are listed in Table 1. Neuropsychological evaluation will not be conducted at T2.

**Table 1 Tab1:** Secondary and other outcome measures

Outcome measure	Measures
Secondary outcomes	
Postconcussive symptoms	Rivermead Post-Concussion Symptoms Questionnaire (RPQ) [31]
Quality of life	EuroQol five dimensions (EQ-5D) [48]
	Quality of Life After Brain Injury instrument (Qolibri) [49]
Other outcome measures	
Fatigue	Fatigue Severity Scale (FSS) [50]
Sleep	Insomnia Severity Index (ISI) [51]
Self-reported cognitive functioning	Cognitive Failures Questionnaire (CFQ) [52]
Emotional functioning (anxiety and depressive symptoms, posttraumatic stress symptoms, and self-efficacy)	The Patient Health Questionnaire (PHQ-9) [53]
	Generalized Anxiety Disorder seven-item (GAD-7) scale [54]
	Posttraumatic Symptom Scale (PTSS-10) [55]
	General Self-Efficacy Scale (GSS) [56]
Neuropsychological test measures	
Learning and memory	California Verbal Learning Test–Second Edition (CVLT-II) [57]
Prospective memory	Memory for Intentions Screening Test (MIST) [58]
Processing speed/executive function	Color Word Interference Test from the Delis-Kaplan Executive Function System (D-KEFS) [59]
	Trail Making Test (TMT) from the Delis-Kaplan Executive Function System (D-KEFS) [59]
	Coding from the Wechsler Adult Intelligence Scale–Fourth Edition (WAIS-IV) [34]
	Ruff 2 and 7 Selective Attention Test [60]
	Modified Six Elements Test from the Behavioral Assessment of the Dysexecutive Syndrome (BADS) (to be applied at T4 only) [61]
Validity	Forced Choice Recognition index from the CVLT-II [57]

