**Methods/design:**

This study protocol describes an innovative randomized controlled trial in which we will explore the effect of combining manualized cognitive rehabilitation (Compensatory Cognitive Training [CCT]) and supported employment (SE) on RTW and related outcomes for patients with mild to moderate TBI in real-life competitive work settings. The study will be carried out in the southeastern region of Norway and thereby be performed within the Norwegian welfare system. Patients aged 18–60 years with mild to moderate TBI who are employed in a minimum 50% position at the time of injury and sick-listed 50% or more for postconcussive symptoms 2 months postinjury will be included in the study. A comprehensive assessment of neurocognitive function, self-reported symptoms, emotional distress, coping style, and quality of life will be performed at baseline, immediately after CCT (3 months after inclusion), following the end of SE (6 months after inclusion), and 12 months following study inclusion. The primary outcome measures are the proportion of participants who have returned to work at 12-month follow-up and length of time until RTW, in addition to work stability as well as work productivity over the first year following the intervention. Secondary outcomes include changes in self-reported symptoms, emotional and cognitive function, and quality of life. Additionally, a qualitative RTW process evaluation focused on organizational challenges at the workplace will be performed.

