A novel approach to vocational rehabilitation based on the “place-then-train principles” in SE involves support in real-life competitive work settings and is aimed at providing professional services to people with disabilities to help them participate in the competitive labor market [26]. The Five-Step Process describes support activities in the inclusion process: engagement, vocational profiling, job finding, employer engagement, and on-/off-job support. The Individual Placement and Support (IPS) Fidelity Scale is based on eight principles: competitive employment, eligibility based on client choice, integration of rehabilitation and health care services, attention to client preferences, personalized benefits counseling, rapid job search, systematic job development, and time-unlimited and individualized support. SE has not been evaluated in RTW for individuals with TBI in the Norwegian context, but IPS has gained empirical support with positive results in terms of both work inclusion and non-work-related outcomes for people with mental illness [27–29]. SE will be implemented in this RCT in combination with CCT. To determine the feasibility of the proposed interventions and the implementation of procedures in a Norwegian context, a feasibility study will be conducted. In the RCT, the effectiveness of a combined cognitive and vocational rehabilitation intervention compared with treatment as usual (TAU; a nonstandardized rehabilitation provided by a multidisciplinary rehabilitation team) will be evaluated.

The following are the main study hypotheses:Combined CCT and SE will result in a faster RTW and better work stability, as well as reduced postconcussive symptoms and improved cognition, than TAU.Combined CCT and SE will result in reduced emotional distress and improved quality of life compared with TAU.Combined CCT and SE will be a cost-effective alternative compared with the TAU condition.Factors related both to the workplace and to the patient’s motivation for RTW will affect the RTW process.

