## Methods/design

### Study design

The proposed study will be a parallel-group RCT with a mixed method in design. Based on the Standard Protocol Items: Recommendations for Interventional Trials (SPIRIT), the study flowchart, standard protocol items, and SPIRIT checklist are provided in Figs. 1 and 2, and Additional file 1, respectively. Once included, participants will undergo a baseline assessment of cognitive and emotional status (T1), with further assessments immediately following the CCT intervention (3 months after study inclusion [T2]), following the end of SE (maximum 6 months after inclusion [T3]), and 12 months after study inclusion (T4). All study assessments will be conducted at Oslo University Hospital (OUH). A process evaluation will be performed to explore participants’ experiences with the intervention, as well as individual and workplace-related mechanisms of importance in the RTW process. A qualitative evaluation study regarding patient experiences with CCT is also being planned.

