### Statistical analysis

Descriptive statistics will be used to describe the baseline and injury characteristics of the variables related to participants and services. The *t* test will be used to analyze between-group mean comparisons for normally distributed continuous data, and the Mann-Whitney *U* tests will be used to analyze skewed data. For the primary outcome measures, a logistic regression model will be used to compare the proportions of participants returning to work at T4 in the CCT-SE and TAU groups, adjusting for other potential confounders. In addition, linear regression analysis will be applied to compare the difference in the mean length to RTW between the intervention groups at T4, adjusting for other potential confounders. For the secondary outcome measures, repeated measures analysis of variance will be used with time (T1–T4) as the repeated-measures factor and group (CCT-SE and TAU) being a between-group factor to test whether the CCT-SE intervention has a beneficial effect compared with TAU on RTW, symptoms, and functioning. The intention-to-treat principle will be applied for all proposed analyses.

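### The abstract and Outcomes disagree on cognitive testing after CCT, and the four-visit ANOVA, if it covers cognition, does not fit the neuropsychological tests' visits

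*Protocol article*

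**What the plan says.** **Schedule.** The abstract (Methods/design) says: "A comprehensive assessment of neurocognitive function, self-reported symptoms, emotional distress, coping style, and quality of life will be performed at baseline, immediately after CCT", and then at 6 and 12 months. Study design is looser: "participants will undergo a baseline assessment of cognitive and emotional status (T1), with further assessments immediately following the CCT intervention", followed by T3 and T4. Outcomes says: "Neuropsychological evaluation will not be conducted at T2". Table 1 marks the Modified Six Elements Test "to be applied at T4 only".

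**Status of cognition.** The abstract counts it as secondary: "Secondary outcomes include changes in self-reported symptoms, emotional and cognitive function, and quality of life". Outcomes is narrower: "Postconcussive symptoms and quality of life will be used as secondary outcome measures at all time points (T1–T4"). Table 1 lists only RPQ, EQ-5D and Qolibri as secondary and puts the neuropsychological tests under their own heading. The first main hypothesis nevertheless expects a faster return to work "as well as reduced postconcussive symptoms and improved cognition, than TAU".

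**Analysis.** For the secondary outcome measures, Statistical analysis states that "repeated measures analysis of variance will be used with time (T1–T4) as the repeated-measures factor", with group as the between-group factor. The stated purpose extends to return to work, symptoms and functioning. The only other comparison that could apply to a test score is the general provision for a t test or a Mann-Whitney test.

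**The concern.** The abstract and Outcomes cannot both be right about objective cognitive testing at T2. A reader of the abstract will expect a between-group comparison of test performance at 3 months, and under Outcomes there will be none.

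The conflict carries into the analysis. Cognition belongs to a main hypothesis, but the article does not say clearly which model serves it. If cognition is secondary, as in the abstract, the named model has a visit at which the tests are not given. If it belongs with the other outcomes, as Table 1 suggests, no longitudinal model is named for it and only the unadjusted two-group comparison remains. In both cases the visits and the model for the tests still have to be chosen. That choice should be fixed before the data are seen, and it should use the baseline scores that the trial already collects.

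**Working it through.** The plan gives no figure on this point to reproduce. The check has three steps.

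**1. Visits by source**

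| Measure | Abstract | Outcomes and Table 1 |
|---|---|---|
| RPQ, EQ-5D, Qolibri | T1, T2, T3, T4 | T1, T2, T3, T4 |
| Neuropsychological tests, except the one below | T1, T2, T3, T4 | T1, T3, T4 |
| Modified Six Elements Test | not named | T4 |

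The entry T1, T3, T4 is what remains of the four assessments once T2 is ruled out.

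**2. Can the stated model be fitted?**

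A group-by-time cell-means model with 2 groups and k visits has 2 × k parameters. It can identify at most one mean per group and observed visit.

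- Four levels, measured at T1–T4: 2 × 4 = 8 parameters and 2 × 4 = 8 observed cells. The rank is 8 of 8, so everything is estimable.
- Four levels, measured at T1, T3 and T4: 8 parameters and 2 × 3 = 6 observed cells. The rank is 6 of 8. The T2 effect and the T2-by-group term are not estimable.
- Four levels, measured at T4 only: 8 parameters and 2 × 1 = 2 observed cells. The rank is 2 of 8. No time effect or interaction is estimable.
- Three levels (T1, T3, T4), measured at those visits: 2 × 3 = 6 parameters. The rank is 6 of 6, and the interaction has (2 − 1) × (3 − 1) = 2 degrees of freedom.

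The ranks were confirmed numerically from the design matrices. The four-level form therefore fits no neuropsychological test. The three-level form fits all of them except the Modified Six Elements Test, which allows only a between-group comparison at T4.

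**3. What would baseline adjustment gain for the T4-only test?**

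The T1 assessment includes the D-KEFS tests and the IQ estimate. If these correlate r with the T4 score within groups, adjustment multiplies the residual variance by 1 − r² and the standard error by √(1 − r²).

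- r = 0.3: 1 − 0.09 = 0.91, and √0.91 = 0.954. The variance falls by 9% and the standard error by 4.6%.
- r = 0.5: 1 − 0.25 = 0.75, and √0.75 = 0.866. The variance falls by 25% and the standard error by 13.4%.

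The article gives no correlation, so the range 0.3–0.5 is an assumption.

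**The case against.** The strongest reply concerns scope. The ANOVA is assigned to the secondary outcome measures. Outcomes and Table 1 define these as postconcussive symptoms and quality of life, measured at all four visits, so model and schedule agree exactly. On that reading the abstract is a loose condensation that the Methods settle. An analyst would simply drop the unmeasured visit, and visit levels per instrument are detail that an article may leave to an analysis plan. A single T4 score can also be compared validly between randomised groups by a t test.

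Much of this stands. The secondary outcomes in Table 1 are not affected, the T1/T3/T4 form works, and the unadjusted T4 comparison is valid. The reply does not remove the contradiction on the schedule, nor the disagreement over whether cognition is secondary. The abstract includes it, and Statistical analysis extends the ANOVA's purpose to functioning.

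A reader might infer more than the article supports:

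- **That no repeated measures analysis of cognition is possible.** This is true only of the four-level form.
- **That Study design also contradicts Outcomes.** It mentions further assessments without saying that the test battery is repeated at T2, so it only implies this. Self-reported cognition (CFQ) is not excluded at T2.
- **That the trial loses its means of isolating the CCT effect.** The hypothesis concerns combined CCT and SE against TAU and names no visit. Limitations already concedes that the components are hard to separate.
- **That some participants will be tested at T2 and carry practice effects forward.** This would require staff to follow the abstract over an explicit instruction in Outcomes, and nothing in the article suggests it.

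**Conclusion.** The point holds in a limited form. The abstract contradicts Outcomes on objective cognitive testing immediately after CCT. Whether the T1–T4 ANOVA covers cognition is unclear. If it does, its four-level form cannot be fitted to any neuropsychological test, while a T1/T3/T4 form can be fitted to all but the Modified Six Elements Test.

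The consequence is moderate. No primary outcome and no secondary outcome in Table 1 is touched, and no bias is shown. What is affected is the cognitive part of the first main hypothesis, which lacks one consistent schedule and a model matched to it. Aligning the abstract alone would be clerical. The worthwhile gain is to use the T1 scores as covariates. For the T4-only test the standard error would be about 5–13% smaller, provided the within-group correlation lies between 0.3 and 0.5.

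**What to change.** 1. **Abstract:** state that the neuropsychological tests are given at T1, T3 and T4 (the Modified Six Elements Test at T4 only), in line with Outcomes. Study design needs no correction, though a clause pointing to Outcomes would help.
2. **Status:** say in one place whether cognition is a secondary or an other outcome, and make the abstract and Table 1 agree.
3. **Statistical analysis, repeated tests:** analyse T3 and T4 as the outcome visits, with the T1 score of the same test as baseline covariate. T1 precedes the intervention, so it serves better as a covariate than as an outcome level.
4. **Statistical analysis, Modified Six Elements Test:** compare the groups at T4 by ANCOVA, adjusted for named T1 D-KEFS scores and the IQ estimate. Choose these covariates before the outcome data are examined.

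The cost is a few changes of wording and one or two model statements. All the covariates are already in the T1 assessment, so no visit or test is added.

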### Process evaluation: qualitative perspective on RTW process

The aim of the qualitative process evaluation is to explore features of the “train and maintain” elements that take place at the workplace during the RTW process (i.e. types of support, as well as if and how the employment specialists manage to generate partnerships with employers for job adjustments and adapt work, job development, and job carving to fit the needs of employees with TBI). Additionally, we will assess how risks, challenging behavior, and conflicts are dealt with, as well as how natural internal company support and increased inclusion competencies within the workplaces may be developed. In line with theory [35], we assume that increased practical knowledge of opportunities and obstacles for work inclusion at the workplace generates increased commitment among the relevant stakeholders. This knowledge and learning process in the work organization may increase the possibility for successful RTW and job tenure. Furthermore, via the qualitative evaluation process, we will seek to identify which managerial styles are most effective in creating secure work environments and promoting successful RTW processes for the targeted population.

The process evaluation will be based on semistructured interviews in individual RTW case processes. Each case process will include three informant groups: participant, workplace employer, and employment specialist (intervention group only) or supervisor at the local office of the public Norwegian Labor and Welfare Service (NAV) (CG only). Interviews will be conducted at two different time points in each case process: 1 month and 12 months following RTW. The interviews will provide an empirical base for additional knowledge on job content and skill requirements (i.e., possibilities for adapted/alternative work tasks); work environment quality (i.e., demands, control, support); the role of management as well as types and features of work organization (i.e., division of tasks, specialization, interdependencies), and what kind of external support is needed (i.e., the employment specialists’ contributions that influence job match achievement and the sustainability of the work relationship).

The contents of the interview questionnaires are developed on the basis of selected elements from the COPSOQ [33], the Multifactor Leadership Questionnaire [36], and the SE Five-Step Process and IPS Fidelity Scale [37, 38]. In the interviews in both the intervention and control groups, we will seek to achieve the following:Identify the employment specialist’s methods as well as cooperation between the employment specialist and the CCT team, the employment specialist and the employer, and the employment specialist and the person with TBIIdentify attributes and workplace conditions (e.g., work tasks/production, internal company training systems, work environment, and management factors) that may influence the RTW processIdentify work organizational indicators for successful RTW and job stabilityIdentify significant changes in individual inclusion and exclusion processes at the work organization levelIdentify effective managerial styles that promote RTW

### Sample size

Regarding RTW, an OR of 2.0 between the Compensatory Cognitive Training–Supported Employment (CCT-SE) and CG is regarded as the smallest relevant clinical and societal OR. Thus, the required total sample size calculated using G*Power is 110 (i.e., 55 persons in each group; α = 0.05, power level of 0.80) [39]. With an estimated loss to follow-up of 15% [40], 125 participants will be required. On the basis of an ongoing TBI study [41], we assume that this will be achievable within 12–18 months. An OR of 2.0 is equivalent to a 33% absolute difference in employment status between the two groups. According to [name] et al. [21], 50% of patients attained competitive work at 12-month follow-up. If the proportion of employed patients in the CG is 50% at 12-month follow-up, the proportion for the intervention group in this study will be expected to be 83% or above on the basis of the given estimation.

Two strategic samples will be drawn for the process evaluation, comprising 40 cases from the intervention group and 20 from the CG. It is a goal to achieve a heterogeneous sample with variation in severity of TBI, sex, age, type of job and workplace, company size, industry, and sector.

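### The stated 110 evaluable participants give about 42% power, not 80%, for the stated OR of 2.0, and 110 does not follow from the 50% v 83% target either

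*Protocol article*

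**What the plan says.** The Sample size section of the protocol article takes an OR of 2.0 for RTW between the two arms, which "is regarded as the smallest relevant clinical and societal OR". From this it concludes that "the required total sample size calculated using G*Power is 110 (i.e., 55 persons in each group", with "α = 0.05, power level of 0.80". It does not say whether alpha is one- or two-sided and does not name the G*Power routine.

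The same paragraph goes on:
- "With an estimated loss to follow-up of 15% [40], 125 participants will be required".
- "An OR of 2.0 is equivalent to a 33% absolute difference in employment status between the two groups".
- "If the proportion of employed patients in the CG is 50% at 12-month follow-up", then "the proportion for the intervention group in this study will be expected to be 83% or above".

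The Randomization section gives 1:1 allocation. The Statistical analysis section says that "a logistic regression model will be used to compare the proportions of participants returning to work at T4", with adjustment for potential confounders.

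**The concern.** The paragraph links four quantities: an OR of 2.0, a sample of 110, an alpha of 0.05 and power of 0.80. With its 50% control rate, everything needed to check the link is on the page, and the link fails. This is not a detail left to an analysis plan; it is a stated result that contradicts its stated inputs.

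The error is separate from the sentence equating an OR of 2.0 with a 33-point difference. Correcting that sentence alone would leave 110 participants, OR 2.0 and 80% power side by side, and still wrong.

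The stake is how the RTW proportion at 12 months, the first-named primary outcome, will be read. If an OR of 2.0 is the true effect, a trial of this size misses it more often than it finds it. A reader who trusts the 80% figure would take a non-significant result as evidence against a relevant benefit, and the article says the project should inform policy makers.

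**Working it through.** **Inputs** (Sample size and Randomization sections): OR 2.0; control rate 50%; 1:1 allocation; 55 per arm; alpha 0.05; power 0.80; 125 enrolled; 15% loss. Two-sided testing is an assumption; one-sided results are also given.

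**Step 1. Intervention rate under OR 2.0.**
p = 2.0 × 0.5 / (0.5 + 2.0 × 0.5) = 0.667, a difference of 16.7 points. By contrast, 50% v 83% is an OR of (0.83/0.17)/(0.5/0.5) = 4.88.

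**Step 2. Attempt to reproduce 110 from OR 2.0.** Two-proportion formula with pooled variance under the null:

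n per arm = [z(α)·√(2·p̄·(1−p̄)) + z(0.80)·√(p₀(1−p₀) + p₁(1−p₁))]² / (p₁−p₀)²

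With p̄ = 0.5833 the two roots are 0.6972 and 0.6872.
- Two-sided: (1.960 × 0.6972 + 0.842 × 0.6872)² / 0.1667² = 136.2, so 137 per arm, 274 in total.
- One-sided: (1.645 × 0.6972 + 0.842 × 0.6872)² / 0.1667² = 107.1, so 108 per arm, 216 in total.
- Two-sided with continuity correction: 148 per arm. Wald test of the log OR, which corresponds to unadjusted logistic regression: 278 in total.

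None is near 110 in total.

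**Step 3. Power at 55 per arm for OR 2.0.**
Φ[(0.1667 × √55 − 1.960 × 0.6972) / 0.6872] = Φ[(1.236 − 1.367)/0.6872] = Φ(−0.19) = 0.425.

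| Method, 50% v 66.7%, 55 per arm | Power |
|---|---|
| Pooled normal approximation, two-sided | 42.5% |
| Wald log OR, two-sided | 42.2% |
| Exact power of Pearson chi-square | 42.1% |
| Fisher exact, two-sided | 34.2% |
| Pooled normal approximation, one-sided | 55.2% |

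**Step 4. Does another control rate rescue it?** Over control rates from 2% to 98%, power for OR 2.0 at 55 per arm never exceeds 43.5% two-sided or 56.2% one-sided.

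**Step 5. Attempt to reproduce 110 from 50% v 83%.** With p̄ = 0.665 the roots are 0.6675 and 0.6254.
- n = (1.960 × 0.6675 + 0.842 × 0.6254)² / 0.33² = 30.9, so 31 per arm.
- Power at 55 per arm = Φ[(0.33 × √55 − 1.960 × 0.6675)/0.6254] = Φ(1.82) = 0.966.

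So 110 does not come from this effect either.

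**Step 6. Effect with 80% power at the stated size.** Setting the power formula in Step 3 to 0.80 and solving for the intervention rate at 55 per arm gives 75.5%, an OR of 0.755/0.245 ≈ 3.1 (one-sided, OR about 2.7).

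**Step 7. The planned enrolment.** 125 × 0.85 = 106.25, about 53 per arm, not 55; 110/0.85 = 129.4, so 130 would have to be enrolled. At 53 per arm, two-sided power for OR 2.0 is 41.2%, and 80% power is reached at 50% v about 76%, OR 0.76/0.24 ≈ 3.2.

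**Step 8. What a non-significant result can exclude.** The 95% CI half-width for the RTW difference at 55 per arm is 1.96 × √((0.25 + 0.2222)/55) = 0.182, or 18.2 points, against an effect of 16.7 points. The interval is centred on the observed difference, so its upper limit falls below 16.7 only when the observed difference is about −2 points or lower. If both true rates are 50%, that happens in about 39% of trials.

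**The case against.** Several counter-arguments deserve an answer.

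- **Sidedness and routine are not given.** This stands as a limit on wording: two-sided 0.05 is an assumption. It does not rescue the figure, because one-sided testing gives 55%. A logistic calculation with a continuous predictor yields totals of 65 to 88 two-sided at a 50% event rate, and it does not describe a two-arm comparison.
- **Covariate adjustment is planned.** The unadjusted calculation is therefore an approximation, but adjustment could not plausibly move power from 42% to 80%.
- **The trial may have been designed for 50% v 83%.** A reader might infer from the 42% that the trial is underpowered for everything it names. The document does not support that: for 50% v 83%, 55 per arm exceed 80% comfortably. The shortfall is for OR 2.0. Which target the sponsor meant cannot be told from the text, so the two must be reconciled.
- **The confidence interval.** Because the half-width exceeds 16.7 points, a reader might infer that no non-significant result could ever exclude the smallest relevant effect. That does not follow, as Step 8 shows: with no true difference, about 39% of trials would exclude it. The supportable statement is that such a result would often fail to do so.
- **Scope.** The article lists several primary outcome measures, and the power statement concerns the RTW proportion only. This point does not extend to time to RTW, productivity or work stability.

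**Conclusion.** The point holds. For the effect that the protocol calls the smallest relevant one, the stated 80% power is about 42% two-sided at 55 per arm, and about 41% at the roughly 53 per arm that the planned enrolment leaves. About 137 per arm would be needed, 274/110 ≈ 2.5 times the stated total.

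The conclusion does not depend on the 50% control rate, since no control rate lifts two-sided power above 43.5%, nor on two-sidedness, since the one-sided maximum is 56.2%. The exact detectable effects do depend on both, and on an unadjusted comparison of two proportions. For control rates of 30% to 60%, the OR with 80% two-sided power at 55 per arm ranges from 2.96 to 3.44.

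The error is in the power statement. It does not bias the estimate of the treatment effect. It affects what a non-significant RTW proportion can be taken to mean.

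**What to change.** Without changing enrolment, in the Sample size section:

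1. State whether alpha is one- or two-sided.
2. Correct the sentence equating an OR of 2.0 with a 33-point difference: from 50%, an OR of 2.0 is 66.7%, or 16.7 points, and 83% is an OR of about 4.9. Say which effect is the design target.
3. Restate the power, for example: *With 125 enrolled and 15% loss (about 53 evaluable per arm), two-sided 0.05, power is about 41% for OR 2.0 (50% v 66.7%) and 80% for 50% v about 76% (OR about 3.2). With 55 evaluable per arm the figures are about 42% and 50% v about 75.5% (OR about 3.1).* If the sponsor declares a one-sided test, recompute these figures.
4. Add that a non-significant result for the RTW proportion at 12 months will be interpreted from the confidence interval for the RTW difference, not as absence of a relevant effect.

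The cost is wording and a less favourable power statement. No extra patients and no change of outcome or analysis are needed.
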